### Overview

Musculoskeletal pain patients will be offered participation in this study until at least 342 patients have been enrolled in baseline assessment and 105 patients have been included into our randomized controlled proof-of-concept study. All 105 patients enrolled in the study will undergo detailed phenotyping before and after intervention, which, together with the response/non-response data from the RCT, will serve to improve the allocation algorithm for future studies. All patients eligible will be randomly assigned 1:1 to a personalized or non-personalized treatment arm (Fig. 1). Personalization is achieved by a targeted allocation either to a therapy focused on emotional distress, a therapy focused on dysfunctional behaviours and maladaptive learning or allocation to a minimal intervention group where adaptive responses to pain will be registered. After baseline assessments (Fig. 1, T_0_) for relevant pathomechanisms, each patient included in the trial will receive either 12 weekly sessions of cluster-matching therapy (intervention arms)—where patients are allocated personalized (i.e. according to their individual pain mechanism)—or non-cluster-matching therapy (control arms) —where they are allocated non-personalized (i.e. randomly assigned between the other two interventions). After the last session, all procedures included in the baseline assessment will be performed as a posttreatment evaluation (Fig. 1, T_1_). Furthermore, a 3-month follow-up by means of telephone interview and questionnaire package will be implemented for patients taking part in the intervention study (Fig. 1, T_2_). At T_2_, the maintenance of the effects on pain and pain-related impairments will be assessed. In order to guarantee a correct evaluation of our primary outcomes in pain change, we will include an extended psychological assessment (details on outcomes are given below).

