#### Pain Extinction and Retraining-tailored (PERT) intervention

PERT is a structured cognitive-behavioural derived intervention that focuses on retraining and alterations of maladaptive brain responses and includes elements such as activity increase, reduction of compensatory behaviours, medication management, altering social interactions, training of pleasant events and improving sensory discrimination. The treatment is based on an extension of a standardized manual [35] and consists of 12 weekly 100-min sessions led by two psychologists and is conducted in groups of 5–6 patients. To ensure a good patient-therapist relationship, all patients will have two individual sessions with the therapist prior to the group therapy. The group therapy includes video feedback of expressions of pain as well as training of pain-incompatible behaviours, increase of work-related and social activities and medication management. Patients are encouraged to participate in role plays to reduce dysfunctional pain behaviour and promote healthy behavioural responses. To increase the transfer of the treatment effects from the clinic to everyday life of the patients, the training also includes several sessions together with their spouses. Spouses will be fully informed and consented just as study participants. In previous studies, we could show that PERT interventions are superior to multimodal pain interventions and that maladaptive brain activation patterns can be altered by such interventions [15, 36–39]. In a study that is currently under review (Thieme, Kleinböhl et al., submitted), we analysed post hoc to what extent a matching of PERT to patients who are highly dysfunctional compared to those who are characterized by traumatic events/high stress/depressive responses or patients who have no specific dysfunctional or stress-related characteristics boost the treatment effect. Patients who happened to receive the fitting personalized treatment showed an almost 2-fold increase in effect size and a 50% reduction in drop-out. In this previous study, we did a post hoc analysis—the aim is now to a priori assign patients based on an optimized treatment algorithm.

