### Sample size calculation

The study will be performed in an exploratory fashion and is planned as a pilot study to describe the feasibility and safety of personalized treatments for CMSP as a primary outcome, as well as an initial estimation of signals efficacy and utility as secondary outcomes. Even though a formal power calculation is not necessary in a pilot study, we nevertheless performed a power calculation to better estimate the initial signals of efficacy and utility.

For power considerations, we use a mixed-model with repeated measurements (MMRM), a two-sided significance level of 5% and a sample size of 90 patients (→45 per study arm →90 total from a total of 105 patients at an assumed dropout rate of 15%). The MMRM takes into account also the interim measurements for each patient and allows therefore a fuller use of the data than an ANCOVA. The sample size of 105 patients allows to calculate our feasibility measures with a 95% confidence interval width from 11 to 19% (for varying proportion 0.1–0.5) based on a Wald interval for binary measures [40]. Moreover, patients with data with at least one measurement can be used for the primary analysis; therefore, we expect fewer patients not to be usable for the analysis compared to an ANCOVA. Between repeated measurements, a correlation of 0.3 is assumed. Then, the study has a power of 80% to detect a true effect size of *f* = 0.22, a power of 85% for *f* = 0.23 and 90% power for a true effect size of *f* = 0.25. Dropouts will be analysed according to the underlying reasons for dropout and distinction will be made between those dropouts that are preventable by modification of study design and those that are not preventable by study design adaptations.

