Feasibility objectives will be quantified. If appropriate, 95% confidence intervals will be calculated based on the Wilson Score interval for binary measures. We favoured the Wilson Score interval against Wald interval due to their good properties for small numbers of trials, compared to Wei and Hutson [40]. For the analysis of the primary outcome, we will use the complete and pseudonymized data set and follow the intention-to-treat approach which includes all patients in the group they were allocated to by randomization. This approach preserves the allocation of treatment by randomization and it will be as close as possible to the ITT ideal of including all randomized patients. As sensitivity analysis, the analysis will be repeated in the per-protocol (PP) set, excluding patients with major protocol violations. Additional sensitivity analyses will explore the effects of the treatments the patients actually received. The null-hypothesis H0 (no difference occurs in the population means with regard to pain severity at T1 between the experimental intervention and the control intervention) will be tested against H1 (there is a difference in the population means of pain severity differences between the two groups at T1 and T0). Provided that the model assumptions are fulfilled, the null hypothesis will be tested using a (robust) mixed linear regression model at a significance level of 5%. The primary outcome (pain severity at T1, difference to T0) will be analysed using mixed-effects model repeated measurements after 4, 8 and 12 weeks (=T1). The analysis will be adjusted for condition, gender and baseline (T0) pain severity. Compound symmetry will be assumed. Because of the exploratory nature of the study, the observed initial signals of efficacy and utility will be considered more important than the *p*-values. The corresponding *p*-values of these tests will be interpreted purely descriptively. We will compute effect sizes and interpret them together with the respective 95% confidence intervals. Regarding secondary endpoints, exploratory data analysis will be performed using appropriate analytical methods depending on the respective parameter. Details of the statistical analyses will be fixed in a statistical analysis plan developed by the statistics department of IZKS Mainz prior to database closure. The safety analysis includes calculation and comparison of frequencies and rates of adverse events. Furthermore, statistical methods are used to assess the quality of data and the homogeneity of intervention groups. All analyses will consider gender aspects. Prior to all analyses, we will pre-specify a statistical analysis plan.

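### Compound symmetry is fixed, with no fallback, for a hypothesis about week 12 alone, so the T1 confidence interval may have the wrong coverage if residual variance differs between visits

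*Protocol article*

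**What the plan says.** All of the following is in the protocol article.

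- *Statistical analyses*: the tested difference is in pain severity at T1 relative to T0. The model is a mixed model for repeated measurements at weeks 4, 8 and 12, where week 12 is T1. The adjustment terms named are condition, gender and baseline pain severity. On the covariance: "Compound symmetry will be assumed". No other structure is named as a fallback.
- The same section makes use of the model conditional on its assumptions holding and attaches the word robust in parentheses, without saying whether this means a sandwich variance or an outlier-resistant fit. P-values are to be read descriptively. On estimation: "We will compute effect sizes and interpret them together with the respective 95% confidence intervals". Further detail is left to a statistical analysis plan.
- *Sample size calculation*: "a two-sided significance level of 5% and a sample size of 90 patients", then "Between repeated measurements, a correlation of 0.3 is assumed", with 80%, 85% and 90% power at f = 0.22, 0.23 and 0.25.
- *Objectives*: feasibility and safety are primary, and efficacy is an initial estimate.

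**The concern.** Compound symmetry imposes one variance at every visit and one correlation between any two visits. That matters little for an effect averaged over visits, but it does matter for a contrast at a single visit. The model then estimates one residual variance from weeks 4, 8 and 12 together and uses it for the week-12 comparison. If week-12 variance lies above that average, the interval is too narrow. If it lies below, the interval is too wide.

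Two features of the plan make a rise towards week 12 plausible. The trial's premise is that some patients respond well and others do not improve, which would spread scores as therapy proceeds. The model also adjusts for baseline pain. If correlation with baseline fades over time, baseline explains less at week 12 than at week 4, so residual variance grows even when raw SDs are equal at all visits.

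The interval is the efficacy output that the plan says it will interpret. The pilot is meant to prepare a multicentre trial, so misplaced precision in the T1 effect could carry into that trial's planning.

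**Working it through.** **Inputs from the article.** Analysed N = 90 (45 per arm), two-sided 5%, 1:1 allocation, common correlation 0.3, visits at weeks 4, 8 and 12.

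**Inputs not in the article, therefore assumed.** Residual SDs by visit, and how fast correlation decays.

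**Step 1: reproduce the stated power.** For a between-arm effect averaged over m visits, the noncentrality is λ = f²·N·m / (1 + (m − 1)ρ), with 1 and 88 degrees of freedom. With m = 3 and ρ = 0.3:

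| f | λ | Power | Stated |
|---|---|---|---|
| 0.22 | 0.0484 × 270 / 1.6 = 8.17 | 80.7% | 80% |
| 0.23 | 0.0529 × 270 / 1.6 = 8.93 | 84.0% | 85% |
| 0.25 | 0.0625 × 270 / 1.6 = 10.55 | 89.5% | 90% |

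The stated figures reproduce, as a three-visit average under one exchangeable correlation. Compound symmetry therefore matches the planning model. It need not suit a week-12 contrast.

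**Step 2: standard error at T1.** With a condition-by-visit term and complete data, the T1 estimate is the (adjusted) difference in week-12 means. Its true standard error is √(2σ₁₂²/45). The compound-symmetry model reports √(2σ̄²/45), where σ̄² is the mean of the three visit variances. So:

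- ratio r = reported SE / true SE = √(σ̄²) / σ₁₂
- coverage ≈ 2Φ(1.96 r) − 1

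| Assumed SD, weeks 4:8:12 | σ̄² | r | Coverage |
|---|---|---|---|
| 1:1:1 | 1.000 | 1.000 | 95.0% |
| 0.8:0.9:1 | (0.64 + 0.81 + 1)/3 = 0.817 | 0.904 | 92.3% |
| 0.7:0.85:1 | (0.49 + 0.7225 + 1)/3 = 0.738 | 0.859 | 90.8% |
| 0.6:0.8:1 (extreme) | (0.36 + 0.64 + 1)/3 = 0.667 | 0.816 | 89% |
| 1.2:1.1:1 (falling) | (1.44 + 1.21 + 1)/3 = 1.217 | 1.103 | 96.9% |

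**Step 3: simulation with dropout.** REML fit, 52 per arm, 15% monotone dropout, 3,000 runs per case (Monte Carlo error √(0.95 × 0.05 / 3000) ≈ 0.4 points):

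- compound symmetry true, ρ = 0.3 or 0.6: 94.9% and 95.3%
- AR(1) residual correlation 0.7, equal residual variances: 95.1%
- AR(1) 0.7, SD 0.8:0.9:1: 92.8%
- AR(1) 0.7, SD 0.7:0.85:1: 90.8%
- AR(1) 0.7, SD 1.2:1.1:1: 97.1%

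Unequal variance drives the error. A decaying correlation among residuals of equal variance does no harm.

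**Step 4: baseline decay with equal raw SDs.** Let correlation be c per 4 weeks, starting from baseline, with baseline adjusted separately at each visit. Residual variances at weeks 4, 8 and 12 are 1 − c², 1 − c⁴ and 1 − c⁶.

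| c | Residual variances | r | Closed form | Simulated, compound symmetry |
|---|---|---|---|---|
| 0.6 | 0.64, 0.87, 0.95 | 0.928 | 93.1% | 93.0% |
| 0.7 | 0.51, 0.76, 0.88 | 0.902 | 92.3% | 92.4% |
| 0.8 | 0.36, 0.59, 0.74 | 0.873 | 91.3% | 91.3% |

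The simulation used N = 90, complete data and 20,000 runs. An unstructured covariance gave 94.8-95.0% in these cases. With a constant correlation of 0.3, both structures gave 95%, so the freer structure cost essentially nothing.

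**The case against.** The strongest reply is that nothing in the article shows the visit variances to be unequal. That stands. The error can be zero, and it is conservative if variance falls. A reader might infer that the model is known to be misspecified and the intervals known to be too narrow, but the article gives no visit-specific SDs to support that.

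Second, the article conditions the model on its assumptions and calls it robust. If that means a sandwich variance, the T1 standard error is largely protected against a wrong visit covariance. This stands as a possibility. It does not settle the matter, because the term is undefined and no alternative is named if the assumptions fail.

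Third, the mechanism needs a condition-by-visit term, and only condition, gender and baseline are named. With a condition main effect only, simulation (45 per arm, balanced complete data, rising and falling SDs, correlations 0.3 and 0.6) gave 94.8-95.3% coverage. That is correct, but such a model estimates an average over visits, whereas the stated hypothesis is about T1. To answer the stated question from this model, the interaction is needed.

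Fourth, deferral to an analysis plan excuses missing detail. Here, though, the structure is stated, not left open.

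A reader might also infer an error from therapy groups, since PERT "is conducted in groups of 5–6 patients" and no group term appears. This is not supported as an error: an article may leave such a term to the analysis plan, PERT is given in both arms, and whether groups mix the arms is not stated. With one third of patients in PERT and an assumed ICC of 0.05 or 0.10, coverage is 95.6% or 95.2% if groups mix the arms, and 94.2% or 93.1% if each group is single-arm.

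**Conclusion.** The point holds as a conditional risk in a stated choice. Compound symmetry is fixed without a fallback, and with the robust option undefined, for a hypothesis at one visit. Given a condition-by-visit term and model-based standard errors, the nominal 95% interval at T1 loses about 2-4 points of coverage if residual variance rises moderately towards week 12, and up to about 6 at the most extreme SD ratio tried. It gains about 2 points if variance falls and is exact if variances are equal. A rise is plausible from fading baseline correlation alone, but its size is assumed.

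The consequence is limited, because efficacy is an exploratory secondary aim and p-values are descriptive; inflated type I error is therefore not the right way to express the harm. What is at risk is the stated precision of the T1 effect. Confidence is moderate.

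**What to change.** In the analysis plan, replace compound symmetry by an unstructured covariance over weeks 4, 8 and 12. Include visit and condition-by-visit terms, so that T1 is estimated directly, and use Kenward-Roger degrees of freedom. If the fit does not converge, fall back to a structure that still allows a different variance at each visit. Say what robust means.

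An unstructured matrix for three visits has six parameters against about 90 patients, so it is affordable. The cost is the wording and possibly a slightly wider T1 interval.

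Optionally, record the PERT group identifier in the eCRF and add a PERT-group random effect as a sensitivity analysis. With one third of 90 patients in groups of 5, that is about 6 groups, so the group variance would be imprecise and should not drive the main analysis.

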### Objectives

The primary objective of this study is to investigate the feasibility and safety of a personalized pain psychotherapy approach with three different treatment modules—EDDT, PERT and EMDI. A secondary objective is the initial estimation of efficacy and utility of such a personalized approach compared to a non-personalized approach on different core pain outcome domains.

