As this pilot study compares a personalized treatment allocation based on patient characteristics with a non-personalized treatment allocation, the same treatment interventions are applied in both study arms. However, arms differ in the assignment to the respective treatment modules. In the personalized assignment arm, patients with high level of emotional distress receive an emotional distress-tailored intervention (EDDT: Emotional Distress Desensitization-tailored treatment), patients with high avoidance/maladaptive-learning behaviour receive an exposure/extinction-tailored treatment intervention (PERT: Pain Extinction and Retraining-Tailored Intervention) and patients with neutral risk profile receive a low-level smartphone-based intervention (EMDI: Ecological Momentary-tailored Low-Level Diary Intervention). For every intervention, a special standard operation procedure (SOP) protocol is written regarding the 12-week design and special psychological/pain characteristics of the patient groups. Patients in the non-personalized arm receive a non-personalized intervention allocation (e.g. patients with a high level of emotional stress receive either exposure/extinction-tailored or a low-level smartphone-based intervention, but not the emotional stress-tailored treatment). For this study, matching to the subtypes will be based on a cluster analysis of the West Haven-Yale Multidimensional Pain Inventory (MPI) as well as the age and gender of participants, which have been identified as significant predictors of MPI clusters in previous research. Cluster status of individual participants will be identified by using soft k-means clustering of previous data collected from CMSP patients by the study teams. Using this data, clusters were identified, and the most likely cluster status for participants in the current study will be determined by an automated script implemented in an electronic data collection tool (REDCap) using a random-forest decision algorithm using the established clustering algorithm. Based on this algorithm, participants in the intervention arm will be assigned to the intervention that best fits according to their cluster, while patients in the control arm will be randomly assigned to one of the interventions that do not fit their cluster.

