### Randomization and allocation

For the allocation of the participants, a computer-generated list of random numbers will be used. Randomization for the pilot study will be carried out by the Interdisciplinary Center for Clinical Trials (IZKS) Mainz using permuted blocks of variable lengths. The randomization lists will be implemented in the electronic case report form system (eCRF) such that randomization can be performed electronically as new participants are added to the study. After providing informed consent and the acquisition of baseline data, participants will be randomly assigned to experimental intervention (personalized allocation) or control intervention (non-personalized allocation) via this eCRF system. Allocation will be managed by an independent study manager involved neither in sequence generation, assessments or treatment. All processes will be monitored and controlled for correctness by the IZKS Mainz. This process will be started only after the enrolled participants will have completed all baseline assessments and it is time to allocate the intervention. Randomization will be stratified by cluster, so that patients have a 50% chance of being allocated to the treatment matching their cluster, and 50% of being allocated to one of the two interventions (25% chance each) not matching their cluster.

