
To more closely assess the ecological validity of our design in a naturalistic setting, a second analysis will be carried out where 1/3 of matched patients are randomly sampled and statistically reallocated to the non-matching arms. This is to allow a comparison between personalized treatment and truly random assignment (rather than matched vs non-matched), which may more closely mirror the ultimate implementation of personalization methods in clinical services or during a confirmatory multi-centre RCT.

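### Reallocating one third of the matched patients gives a comparator that is 25% matched, not the 33.3% that random assignment over three modules implies

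*Protocol article*

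**What the plan says.** The last paragraph of Statistical analyses states that "a second analysis will be carried out where 1/3 of matched patients are randomly sampled and statistically reallocated to the non-matching arms". Its purpose is given in the next sentence: "This is to allow a comparison between personalized treatment and truly random assignment (rather than matched vs non-matched"). The protocol adds that this comparison may be nearer to clinical use or to a confirmatory multicentre trial.

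The design features that decide whether the fraction works are stated elsewhere:

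- Objectives: a "personalized pain psychotherapy approach with three different treatment modules—EDDT, PERT and EMDI".
- Overview: "All patients eligible will be randomly assigned 1:1 to a personalized or non-personalized treatment arm".
- Randomization and allocation: within cluster, "patients have a 50% chance of being allocated to the treatment matching their cluster, and 50% of being allocated to one of the two interventions", at 25% each.
- Treatment personalization: "patients in the control arm will be randomly assigned to one of the interventions that do not fit their cluster".

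**The concern.** Under random assignment to three modules with equal probability, a patient lands on the matching module one time in three. One third is therefore the share of matched patients that the comparison group should contain. The protocol applies it to a different denominator, the matched arm. Because the moved patients join a control arm of equal size that holds no matched patients, the resulting share is lower than one third.

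A comparator with too few matched patients lies too far from the personalized group, so the analysis overstates the gain from personalization over random allocation. Statistical analyses puts more weight on the observed signals, with effect sizes and 95% CIs, than on p-values, so the error falls on the quantity that will be read. The pilot is also meant to prepare a larger trial. As an illustration only, since the protocol does not say it will size that trial on this contrast: a trial planned for 80% power at 0.75D when the truth is 0.667D would have (0.667/0.75)² = 79% of the patients it needs. Its power would be about 70% (2.80 × 0.889 − 1.96 = 0.53 on the normal scale).

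**Working it through.** **Inputs.** Three modules (Objectives). 1:1 allocation (Overview). Within cluster, 50% matched and 25% in each non-matching module (Randomization and allocation). No matched patients in the control arm (Treatment personalization). 105 randomized and 90 analysed, 45 per arm (Sample size calculation; 105 × 0.85 = 89.25, which agrees with 90). Assumption: random assignment means equal probability over the three modules.

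**The rule as written.** With arms of equal size n, moving a share s of the matched arm gives a comparator of n + sn patients, of whom sn are matched. The matched share is s/(1 + s), whatever n is.

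- s = 1/3: (1/3)/(4/3) = 25%.
- 45 per arm: 15 moved, comparator 60. Of these, 15/60 = 25% are matched and 22.5/60 = 37.5% are in each non-matching module; 30 remain personalized.
- 105 randomized: 52 matched and 53 control gives 17.33/70.33 = 24.6%; 53 and 52 gives 17.67/69.67 = 25.4%.

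The one third does not reproduce its own aim of 33.3%.

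**The fraction that would.** s/(1 + s) = 1/3 gives s = 1/2. With 45 per arm, 22.5 are moved and the comparator is 67.5, with 22.5 (33.3%) in each of the three modules. With 105 randomized, moving half gives 32.9% (26/79) or 33.8% (26.5/78.5).

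**Other readings of the sentence.** Keeping the sampled patients in the personalized group as well leaves the comparator at 25%. Moving one third of all 90 patients gives 30/75 = 40%. Neither gives 33.3%.

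**Effect on the estimate.** A comparator with matched share m has expected contrast (1 − m)D.

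- As written: (1 − 0.25)D = 0.75D.
- Target: (1 − 1/3)D = 0.667D.
- Ratio: 0.75/0.667 = 1.125, a 12.5% relative overstatement; the difference is 0.083D.

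**Absolute size, by illustration.** Take the protocol's 80%-power effect f = 0.22 and assume the two-group conversion d = 2f = 0.44. The error is 0.083 × 0.44 ≈ 0.04 SD.

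**Precision (45 per arm, outcome SD 1, one measurement, no covariates).**

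| Approach | Groups | SE | Draw-to-draw SD |
|---|---|---|---|
| Move 1/3, one draw | 30 vs 60 | √(1/30 + 1/60) = 0.224 | 0.158 |
| Move 1/2, one draw | 22.5 vs 67.5 | √(1/22.5 + 1/67.5) = 0.243 | 0.199 |
| Weighted contrast | 45 vs 45 | (2/3)√(2/45) = 0.141 | none |

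The draw-to-draw SD is the spread of the estimate over different random samples from the same data. It is √[k(1 − k/45)] × [1/(45 − k) + 1/(45 + k)] for k moved patients; simulation for k = 15, 22 and 23 agrees.

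**Averaging over draws.** For simple means, both the patients who stay and those who are moved have, on average over draws, the full matched-arm mean. The averaged estimate therefore tends to 0.75 × (matched − non-matched) when one third is moved and to 2/3 × (matched − non-matched) when one half is moved. Repeated draws remove the noise but do not correct the fraction.

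**The case against.** The strongest reply concerns weight. The primary objective is feasibility and safety, efficacy is an initial estimation, and this is a second analysis within that part. P-values are to be read descriptively and no feasibility criterion in Outcomes uses the contrast. An error of about 0.04 SD is small beside a standard error of about 0.22 SD, and it vanishes if D is zero. All of that stands, and it limits the severity.

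A second reply is that the protocol states no target share for random assignment. This is true, but it does not rescue the fraction. For 25% to be right, random assignment would have to give the matching module 25% and each other module 37.5%, and nothing in the protocol suggests such a ratio.

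A reader might also infer that the result will hang on one arbitrary random draw. The text describes random sampling without saying how often, and it defers details to a statistical analysis plan that is not shown and may specify repeated draws. Draw dependence is therefore a secondary point. A reader might likewise infer that patients are thrown away. They are not: they move to the comparator and stay in the data, although the personalized group shrinks.

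**Conclusion.** The stated fraction is wrong for its stated purpose. One third of the matched arm yields a comparator that is 25% matched instead of 33.3%, and the analysis estimates 0.75D instead of 0.667D, a 12.5% relative overstatement in favour of personalization when D is favourable. This rests on 1:1 allocation, three modules, no matched patients in the control arm, and equal probabilities under random assignment. The first three are explicit in the protocol and the last is its natural reading. The result does not depend on the sample size.

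Severity is minor to moderate. It would go too far to conclude that the trial's main comparison or its feasibility conclusions are compromised: the matched versus non-matched analysis does not use the reallocation, and neither do the feasibility and safety outcomes.

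**What to change.** Replace the reallocation with a weighted contrast: matched mean minus (1/3 matched mean + 2/3 non-matched mean). This equals 2/3 × (matched − non-matched), so the estimate and both limits of its 95% CI are the main result multiplied by 2/3. It also holds within each cluster, because control patients are allocated equally to the two non-matching modules. It uses all patients and needs no random draw. The plan should state that it rescales the main comparison and adds no independent information to it.

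If reallocation is kept, change the fraction to one half, sample within cluster and average over many draws. The drawback is a smaller personalized group (22.5 instead of 30 with 45 per arm) and lower precision for a single draw (SE about 0.24 against 0.22 SD).

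The cost is about one sentence in the protocol or the statistical analysis plan, which is to be fixed before database closure. The reported personalized-versus-random contrast will be closer to zero, by one ninth (0.667/0.75 = 0.889).
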